## Abstract

**Background:**

Satisfactory treatment is often lacking for spasticity, a highly prevalent motor disorder in patients with spinal cord injury (SCI). Low concentrations of riluzole potently reduce the persistent sodium current, the post-SCI increase in which contributes to spasticity. The repurposing of this drug may therefore constitute a useful potential therapeutic option for relieving SCI patients suffering from chronic traumatic spasticity.

**Objective:**

RILUSCI is a phase 1b–2b trial designed to assess whether riluzole is a safe and biologically effective means of managing spasticity in adult patients with traumatic chronic SCI.

**Methods:**

In this multicenter double-blind trial, adults (aged 18–65 years) suffering from spasticity after SCI (target enrollment: 90 participants) will be randomly assigned to be given either a placebo or a recommended daily oral dose of riluzole for two weeks. The latter dose will be previously determined in phase 1b of the study by performing double-blind dose-finding tests using a Bayesian continuous reassessment method. The primary endpoint of the trial will be an improvement in the Modified Ashworth Score (MAS) or the Numerical Rating Score (NRS) quantifying spasticity. The secondary outcomes will be based on the safety and pharmacokinetics of riluzole as well as its impact on muscle spasms, pain, bladder dysfunction and quality of life. Analyses will be performed before, during and after the treatment and the placebo-controlled period.

**Conclusion:**

To the best of our knowledge, this clinical trial will be the first to document the safety and efficacy of riluzole as a means of reducing spasticity in patients with chronic SCI.

**Trial registration:**

The clinical trial, which is already in progress, was registered on the ClinicalTrials.gov website on August 9, 2016 under the registration number NCT02859792.

**Trial sponsor:**

Assistance Publique–Hôpitaux de Marseille.

## Introduction

Spasticity, one of the most disabling motor impairments, has several pathological causes [such as spinal cord injury (SCI), stroke, multiple sclerosis, cerebral palsy, etc.] [1–3] and affects more than 12 million people worldwide. Spasticity has been mainly defined as heightened muscle tone (hypertonia) due to a velocity-dependent increase in the tonic stretch reflexes [4]. Spasticity is a highly prevalent medical condition occurring after SCI, in particular. It develops in approximately 75% of patients up to one year after SCI [5, 6]. Spasticity can impair patients’ ability to perform activities of daily living by decreasing their mobility, and can also result in symptoms such as pain, sleep disturbances and depression. While antispastic medications can be helpful, no single medication has a beneficial effect in all individuals and each medication has potentially serious side effects [7–10]. When this treatment no longer suffices or is poorly tolerated, no other effective means of treating generalized spasticity are available. There therefore exists a clinical need to improve the management of spasticity.

### Overview of the clinical management of spasticity after SCI

When spasticity becomes troublesome, the therapeutic options available include various pharmacological and non-pharmacological approaches [7, 11, 12]. It is generally agreed that physical rehabilitation is an essential component in the management of spasticity as the first line of defense [13]. As an adjunct to physical rehabilitation, peripheral chemical denervation induced by the intramuscular injection of botulinum toxin (BoNT/A) has been found to relieve focal spasticity effectively, but the effects wear off within about 3 months [14]. Systemic pharmacological drugs for treating spasticity are often prescribed to SCI patients [10]. Baclofen is often the first-line medication used to treat spasticity, for example, but it can be necessary to switch to other medications because of the side effects, the commonest of which are drowsiness (7–70%), excessive weakness (1–69%), somnolence (4.5–70%), vertigo (4.5–13%) and psychological disturbance (1.7–19%) [15, 16]. The rate of treatment discontinuation due to intolerable adverse effects has been reported between 4 to 27%. The main risks of oral baclofen administration are related to withdrawal: seizures, psychic symptoms and hyperthermia can occur [16]. In some cases, an intrathecal delivery can be envisaged. This is obviously an invasive and expensive treatment which requires careful selection of the patients. It is worth noting in particular that withdrawal of baclofen can lead to a severe rebound of spasticity. It is therefore important to take into account the risks associated with the medication prescribed, depending on the patients’ comorbidities. In view of these problems, efforts to expand the range of antispastic drugs available are now urgently required in order to be able to dispense more closely tailored medical solutions, depending on individual patients’ condition. For this purpose, we have adopted Sir James Black’s famous strategy, as stated in 1988: “*The most fruitful basis for the discovery of a new drug is to start with an old drug*”. In line with this statement, we must be able to identify new therapeutic opportunities for treating spasticity based on previously existing approved drugs.

### Pathophysiology of spasticity and the reasons for repurposing riluzole as an antispastic drug

Maladaptive mechanisms promoting a generalized spinal hyperexcitability take place after SCI, and typical signs of spasticity then appear [17–19]. Impaired electrophysiological properties of sublesional neurons are closely involved in the emergence of spasticity [20]. In particular, a switch in the excitability of neurons innervating muscles (motoneurons) from the hypoexcitable state during spinal shock to the hyperexcitable state often occurs several weeks to months after SCI [19–23]. This switch induces motoneurons to express a self-sustained spiking activity triggered by a prolonged state of depolarization known as a *“plateau potential”* [24, 25]. Therefore, plateau potentials constitute a sustained excitatory drive that causes motoneurons to fire beyond the offset of the relevant stimuli, and ultimately generate the exaggeratedly strong, sustained motor responses typical of spasticity [23, 24, 26]. In a series of publications, we have established that the persistent Na^+^ current (*I*_NaP_) is largely expressed in the spinal locomotor network [27–32] and plays a critical role in generating self-sustained spiking activity in motoneurons [30]. SCI upregulates *I*_NaP_, leading to muscle spasms and hyperreflexia in both humans and adult rats [33–39]. In addition, a concomitant synaptic disinhibition of motoneurons due to a decrease in the levels of the main chloride extruder KCC2 also takes place after SCI in both humans and adult rodents [40–42]. We recently established that calpains, which are Ca^2+^-activated proteases recruited after SCI, typically cleave both sodium (Nav) channels, increasing *I*_NaP_, and KCC2, disinhibiting motoneurons [18]. We have therefore assumed that calpains together with KCC2 and *I*_NaP_ might be suitable therapeutic targets for reducing spasticity after SCI. Interestingly, we have established that low concentrations of riluzole specifically and potently block *I*_NaP_, and we have provided strong preclinical evidence in favor of the application of this drug to chronic SCI subjects [18, 38]. More specifically, acute administration of a single dose of riluzole reduces spasticity in rats with chronic SCI. Similar effects have been observed in humans with chronic SCI [39]. Therefore, the chronic administration of riluzole seems to be a potentially useful form of oral medication for obtaining long-lasting relief of spasticity in patients with SCI. The repurposing process should be facilitated as rilutek (the brand name for riluzole) is the only disease-modifying drug approved so far for attenuating neurodegeneration in amyotrophic lateral sclerosis [43]. In addition, a successful phase 1 clinical trial has shown that riluzole taken orally is well tolerated in patients with acute SCI [44–46]. The European Medicines Agency has given Riluzole the status of orphan drug for the treatment of spasticity following SCI. To provide an ever-broadening range of treatment options for reducing spasticity after SCI, we have designed the phase 1b/2b clinical study protocol (RILUSCI) presented here in order to examine the safety and efficacy of orally administered riluzole in patients with chronic SCI.

## Methods and analysis

### Study aims

The primary objectives of the trial will be to define the minimal effective dose of riluzole for treating spasticity, and to assess how effective it is as a means of reducing spasticity. The secondary objectives will be to examine the possible dose/effect relationship and to determine the safety and the pharmacokinetic profile of riluzole, as well as its impact on muscle spasms, pain, health-related quality of life and the mobility of SCI participants.

### Study design

RILUSCI is an adaptive phase 1b–2b trial conducted on spastic patients with chronic SCI in order to determine the potential benefits of administering riluzole as compared with placebo. The protocol has been designed in keeping with the SPIRIT and CONSORT statements (see S1 Checklist: CONSORT 2010 and S2 Checklist: SPIRIT 2013 checklist). The SPIRIT schedule on enrolment, interventions and assessments is presented in **Fig 1**. **Fig 2** is a flowchart of the participants in the study based on the CONSORT guidelines [47].

**Fig 1 pone.0276892.g001:**
[figure not shown]
Standard protocol items recommended for interventional trials (SPIRIT). Schedule of enrolment, intervention and assessments. The study schedule will be the same in step 1 and in step 2 and it includes the following visits and clinical examinations. Patients with chronic SCI will undergo a screening period (v1) with a maximum duration of 2 weeks and then they will be randomized to one of the two groups (v2): riluzole twice daily or placebo twice daily for a 2 weeks period. Three follow up visits are planned: at day3 after the beginning of treatment for PK analysis (v3), and at the end of the 2 weeks treatment period (v4) and one week after withdrawal of study medication (v5).

**Fig 2 pone.0276892.g002:**
[figure not shown]
CONSORT diagram.

Phase 1b will be a single-center double-blind trial involving a continuous reassessment method based on Bayesian inferences. The principle underlying this method is to identify the appropriate drug dosage required to obtain a level of efficacy which resembles as closely as possible a predetermined target level of efficacy in the population. The aim will be to determine the minimal effective dose (MED) of riluzole recorded in 75% of the patients tested. The phase 1 trial will be conducted at the Physical Medicine and Rehabilitation departments of Marseille’s public hospital group.

Phase 2b will be a parallel placebo-controlled multicentre randomised double-blind trial designed to compare the effects of a BID per os treatment with riluzole (daily dose to be defined during Phase 1b) *versus* placebo in participants with chronic SCI. Double-blind conditions will apply to both participants and investigators. The phase 2b trial will be conducted at 7 hospitals all over France. The participating centres include the Physical Medicine and Rehabilitation departments of Marseille’s public hopitals and the Valmante University Institute of Rehabilitation in Marseille (UGECAM), the University Hospitals of Limoges, Montpellier, Nantes, the Propara Rehabilitation centre in Montpellier, and the Saint Martin Rehabilitation Centre in Marseille.

### Participants and recruitment

Participants will be screened and recruited among outpatients consulting for SCI at the various centres participating in the trial during a period of 36 months. Patients’ associations will be contacted by the OrphanDev network (FCRIN) and patients referred by these associations will benefit from a phone interview to check the main inclusion/non-inclusion criteria before being referred to the nearest investigation centre. Participants must meet the following inclusion criteria at the time of the screening visit:

Chronic traumatic spinal cord injury defined as:
◦ Lasting for at least 12 months◦ Level C4-T12◦ Complete or incomplete SCI (ASIA A, B, C, D)◦ With spasticity (MAS > 1 and <5 on adductors and/or sural triceps and NRS > 4Male or Female patients affiliated to the French national health systemPatients aged between 18 and 65. The rationale for limiting the participant’s age to 65 was the poor functional recovery in older individuals [48].Judged by the investigator to be capable of undergoing all the assessments completing all the questionnaires used in the studyThe last injection of BTX-A must have occurred more than 3 months before taking part in the trial and the participants must have regained a comparable level of spasticity to their previous level.The last intrathecal injection of baclofen or the intake per os of any other muscle relaxant must have taken place more than 14 days previously (phase 1b) or be stable for at least 30 days before the screening visit (phase 2b) and must remain stable throughout the protocol.The intake of all other medications, including painkillers, must have been stable for at least 30 days prior to the screening visit.The number of rehabilitation sessions and the methods used should not vary during the 15 days prior to the screening visit.Participants must give their prior informed written consent to the procedure used in the trial.

The exclusion criteria include:

Occurrence of spinal cord injury less than 12 months previously,Any associated brain lesion liable to be the cause of spasticity,MAS≤1 or = 5 in at least adductor muscles and/or sural triceps muscles or NRS < 4Presence of urinary infection, fever, pressure ulcer or other spasticity-aggravating factors.Presence of other significant neurological or mental disorder or other illness liable to prevent accurate evaluation,Recent history (less than 1 year) of chemical substance dependency or any significant psychosocial disturbance,Insufficient fluency in the local language for the patient to be able complete neuropsychological, global and spasticity assessments.Active liver disease or clinically proven jaundiceActive malignancy or history of invasive malignancy within the last five yearsClinically significant neutropenia in the investigator’s opinion, Liver enzymes (ALT/SGPT or AST/SGOT) twice the upper normal limit at screening visit, Baseline elevations in several liver function tests (especially elevated bilirubin) which are clinically significant in the investigator’s opinion.AIDS or AIDS-related complex,The systolic blood pressure measurements > 190 or < 85 mm Hg and/or the diastolic blood pressure measurements > 105 or < 50 mm Hg at screening.An abnormal ECG at screening judged by the site investigator to be clinically significant.Treatment with any investigational drugs or devices less than 60 days before screeningAny myorelaxant medication including intrathecal baclofen taken by the subject during the last 14 days prior to screening (step 1)Patient’s condition not stable under intrathecal baclofen or per os myorelaxant medication for at least 30 days prior to screening (step 2)Patient’s condition not stable under any other chronic medication, including analgesics, for ≥ 30 days prior to screening.Injection of BTX-A into striated muscle less than 3 months previously (apart from BTX-A injection into the detrusor)Subject is currently using, and will continue to use for the next 14 days, any of the following medications, which are classified as Inhibitors of CYP 1A2 (diclofenac, diazepam, nicergoline, clomipramine, imipramine, fluvoxamine, phenacetin, theophylline, amitriptyline and quinolones) or inducers of CYP 1A2 (rifampicin and omeprazole)Ongoing pregnancy and women with childbearing potential not using any form of efficacious contraception during the study and 3 months after the end of the study.Ongoing lactation and during the 3 months after the end of the study.Known hypersensitivity to riluzole

After checking the inclusion and exclusion criteria, each participant will receive extensive information about the treatment tested, the assessment procedures, the objectives and risks associated with the trial. Prior to the start of medication in the study, participants’ informed consent must be obtained in writing by the investigator. Subjects will be free to withdraw from the study at any time without having to give any explanations or being penalized in any way.

### Justification of sample size

In phase 1b, we will use an adaptive Bayesian design in order to minimize the number of subjects to be included. Because of the characteristics of the continuous reassessment method with Bayesian inferences, the inclusion of 30 subjects has been found to suffice for studies of this kind [49, 50]. Stopping rules will be applied sequentially to stop further inclusions before this number is reached. In phase 2b, the expected number of participants is arbitrary because it depends on the opportunities for recruitment at all the centers involved in the study, and the lack of knowledge about the success rate of riluzole is likely to result in a sample size which is too large for a frequentist approach to be used. The number of participants included during 24 months will be 30 participants per randomized group (i.e., 60 patients in all). Participants in phase 1b might also participate in phase 2b.

### Trial protocol

The timeline of the trial summarized in **Fig 1** will be the same in both 2 phases of the study. Subjects will participate for up to 5 weeks. The first 2 weeks will constitute the screening period, starting on the day the subject signs the Informed Consent Form. At the end of the screening period, participants will be randomized (1:1) to either the riluzole or the placebo groupsfor a 2-week period of treatment. Block randomisation stratified per center will be performed. A 1-week post-treatment period will ensue. It is planned to carry out three follow up visits on each participant: on day 3 after the beginning of treatment, at the end of the 2-week period of treatment, and one week after withdrawal of the medication. Details of the assessments and interventions occurring at each visit are presented in **Fig 1**.

At the screening visit, experimental drugs prepared by the coordinating pharmacy will be distributed to the investigating pharmacy at each study site. For phase 1b, riluzole oral suspension (5 mg/ml) will be prepared in 300 ml vial + syringe. For phase 2b, riluzole oral suspension will be diluted in Orablend SF* with a view to administering the same volume (20 ml) of oral suspension to each group. The investigating pharmacy will prepare clinically indiscernible galenic forms of riluzole and placebo. After being prescribed by the investigator, the treatments will be dispensed to patients at the second visit. All the documents required for drug traceability will be completed by the investigating pharmacist. The pharmacist will report the name of the drug, the dosage and the specific number of allocated drugs dispensed to each patient.

In phase 1b, four doses of riluzole will be tested: 25 mg BID, 50 mg BID; 75 mg BID, and 100 mg BID. The four dosage levels were chosen based on previous studies on amyotrophic lateral sclerosis and acute SCI patients treated with riluzole in the standard regimen [46]. The starting dose of riluzole will be randomly selected by the CIC-EC 1426/FCRIN PARTNERS platform. This dose will be communicated only to the pharmacist responsibe for preparing the experimental treatment in order to ensure the blinding of the investigator and the participant. Patients will take the treatment orally for 2 weeks, twice a day (morning and evening), before meals since co-ingestion of the drug with food can reduce the absorption of the drug by up to 20% [44]. The one-week follow-up period will allow for the elimination of riluzole between phases 1b and 2b. Each response to the treatment will be communicated to the biostatistician in charge of performing the Bayesian analysis. The following doses will be allocated, depending on the results of the statistical analysis performed. Dose level assignment will be determined by the CIC-EC 1426/FCRIN PARTNERS platform. Every two inclusions and in view of the outcomes, the success rates will be updated. Clinicians have attributed initial success rate predictions to each dosage, in the light of their clinical experience and the information available in the literature. The following initial predictions have been made: a dose of 50 mg/day: a success rate of 10%; 100 mg/day: 50%; 150 mg/day: 75%; 200 mg/day: 85%. A target probability of success of 75% will be adopted.

During phase 2b, the minimal effective dose defined in phase 1b will be administered to the patients. The CIC-EC 1426/FCRIN PARTNERS platform will inform the pharmacist (at the Timone Hospital in Marseille) about the treatment to be prepared and delivered to each participant. Patients included in the treatment group will take riluzole orally, BID, for 2 weeks at the established ME dose. The same administration schedule will be applied to the placebo patients. Each investigator, participant and pharmacist will be blinded about the identity of the participants in the intervention.

In phase 1 and 2, two 5-ml blood samples for the riluzole PK study and baclofen observance will be consistently collected prior to riluzole intake and 2 h postdose in order to determine the trough and peak concentrations, respectively, on days 0, 3 and 14 after the initial dose (amounting to 6 samples/participant in all). If possible, samples will be sent on the same day to the laboratory in charge of the pharmacokinetic tests. If this is not possible, all the samples will be frozen and stored at -20°C after the pre-analytic process.

All the drugs currently used to treat chronic SCI participants will be recorded, specifying: the name, dose, regimen, dates of start and end of intake. In step 1, participants will need to stop oral myorelaxant medication 14 days prior to screening and during the study. In this step 2, oral myorelaxant medication of participants should be stable for at least 30 days prior screening. Other treatments, including analgesics should be stable for ≥ 30 days prior to screening. Due to the risk of drug interactions, any drugs that interfere with CYP1A2 will be withdrawn at least 5 half-lives before the patients’ inclusion.

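### Phase 1b is described as blinded to dose, but the only preparation given for it is a single 5 mg/ml suspension without volume matching, so intake volume would track dose level

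*Protocol article*

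**What the plan says.** The Study design section of the protocol article states: "Phase 1b will be a single-center double-blind trial involving a continuous reassessment method based on Bayesian inferences". Under Trial protocol, the starting dose goes only to the preparing pharmacist, "in order to ensure the blinding of the investigator and the participant". The levels are given as "four doses of riluzole will be tested: 25 mg BID, 50 mg BID; 75 mg BID, and 100 mg BID".

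The same section describes the product. For the first phase: "For phase 1b, riluzole oral suspension (5 mg/ml) will be prepared in 300 ml vial + syringe". For phase 2b the suspension is to be "diluted in Orablend SF* with a view to administering the same volume (20 ml) of oral suspension to each group". No dilution step, intake volume or vial count is given for phase 1b. The sentence that follows, on clinically indistinguishable forms, compares riluzole with placebo and does not mention dose levels.

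Outcome measures defines success as a sufficient improvement in either the MAS, which is resistance as felt by the rater, or the 0–10 Numerical Rating Scale (NRS), which the participant scores. Under Trial protocol, success rates are updated after every two inclusions, and the resulting MED becomes the phase 2b dose.

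**The concern.** Withholding a dose code blinds people only if the product does not reveal the dose. With one concentration and a syringe, each level corresponds to its own volume. The article states a remedy for this, dilution to a common volume, but only for the phase that tests a single active dose. The phase that compares four doses has none.

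Both components of success can respond to expectation, and either one is enough. The article itself records that clinicians expect success to rise with dose: their initial predictions are 10%, 50%, 75% and 85% across the four levels. If staff or participants can tell high from low, ratings may move with that expectation. The continuous reassessment method (CRM) cannot separate such movement from a drug effect. What is at stake is the shape of the phase 1b dose-response curve and hence the dose taken into phase 2b.

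**Working it through.** **Inputs** (all from Trial protocol)
- Concentration C = 5 mg/ml, in a 300 ml vial.
- Dose per intake D = 25, 50, 75 or 100 mg.
- Intakes: twice daily for 2 weeks, so 2 × 14 = 28.
- Phase 2b common volume: 20 ml.

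**Check on the plan's own figure.** 20 ml × 5 mg/ml = 100 mg, which is the top phase 1b level. So 20 ml is the volume the top level needs undiluted at the phase 1b concentration. A lower dose reaches 20 ml only if it is diluted.

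**Phase 1b as written.** Volume per intake V = D / C. Total volume T = 28 × V. Minimum number of vials = T / 300, rounded up.

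| Dose per intake | V | T | T / 300 | Minimum vials |
|---|---|---|---|---|
| 25 mg | 25/5 = 5 ml | 140 ml | 0.47 | 1 |
| 50 mg | 50/5 = 10 ml | 280 ml | 0.93 | 1 |
| 75 mg | 75/5 = 15 ml | 420 ml | 1.40 | 2 |
| 100 mg | 100/5 = 20 ml | 560 ml | 1.87 | 2 |

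Volume spans a fourfold range and maps one-to-one to dose. The vial count, if only the minimum is dispensed, separates the two lower levels from the two upper ones but does not identify the level.

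**Could 5 mg/ml be a stock that is diluted later?** Dilution only lowers the concentration, so a common volume that includes the top level must be at least 100/5 = 20 ml. That is 28 × 20 = 560 ml per participant, more than one 300 ml vial. It is feasible with two vials, but the text describes no such step for phase 1b.

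**Phase 1b with the phase 2b method applied.** Concentration = D / 20 ml, which gives 1.25, 2.5, 3.75 and 5 mg/ml. Every participant takes 20 ml per intake and 560 ml in total, and receives two vials (560/300 = 1.87, rounded up). Volume and vial count then carry no information about dose level.

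**The case against.** The best counter-argument is that the volume difference is inferred. The article never gives a phase 1b intake volume or says that volume varies with dose. Telling the dose only to the pharmacist who prepares the treatment, and the Discussion's remark that the pharmacist knows which doses to prepare, both fit a dose-specific preparation. Fill volumes and vial counts are also details that an article may leave to a pharmacy manual. This limits how certain the point can be, but it does not remove it. The article does fix a concentration for phase 1b, and it assigns volume matching to phase 2b by name. As it stands, the preparation described undercuts the blinding claimed.

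A reader might go further and infer that phase 1b is in fact unblinded, that the MED is biased, and that all 30 participants are affected. The documents do not support that:
- A participant sees only their own volume and may not be able to decode it. Nothing says they are told the concentration or the range of levels.
- Nothing says that the MAS rater sees the syringe or vials. It is plausible at a single centre where some intakes are timed around blood sampling and electrophysiology, but it is not stated.
- Under Justification of sample size, stopping rules can end inclusion before 30, so 30 is a ceiling.
- Neither the size nor the direction of any effect on the MED can be calculated from the text.
- If the 1:1 placebo allocation under Trial protocol also covers phase 1b, a volume-matched placebo could still hide active from placebo. The gap concerns dose level. The phase 2b comparison with placebo has its own volume matching.

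**Conclusion.** The point holds as an inconsistency between the dose blinding claimed for phase 1b and the preparation described for it. As written, intake volume would identify the dose level to anyone who sees it and knows the concentration or the range of levels. Because success depends on participant-rated NRS or rater-perceived MAS, dose-related expectation could reach the CRM and the choice of MED, for up to 30 participants.

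This rests on two assumptions: that 5 mg/ml is the concentration as taken, and that no volume matching for phase 1b is specified elsewhere. If the full protocol or pharmacy manual shows a constant volume and vial count across the four levels, only the article's wording needs correcting.

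**What to change.** Leave the dose levels as they are and extend the phase 2b volume matching to phase 1b: the same 20 ml per intake and the same number of vials for every level. State this under Trial protocol.

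If that is not feasible, or for participants already treated, stop describing phase 1b as dose-blinded, have the MAS rated by existing staff who do not see the study drug, and report which participants were treated under which preparation.

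The diluent and the 20 ml volume are already planned, so the main cost is extra pharmacy preparation. Participants at the lower levels would take larger volumes: 20 ml instead of 5, 10 or 15 ml. The article says the trial is already in progress, so a change part-way could leave CRM data collected under different blinding conditions before and after it. That is why the preparation should be reported for each participant.

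### A phase 1b patient who stops an oral myorelaxant for the trial must, on the stated timings, do so before signing consent

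*Protocol article*

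**What the plan says.** All places are in the protocol article.

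- **Washout.** Trial protocol, on concomitant drugs: "In step 1, participants will need to stop oral myorelaxant medication 14 days prior to screening and during the study". The phase 1b exclusion criterion bars any myorelaxant "taken by the subject during the last 14 days prior to screening (step 1"). The matching inclusion criterion is slightly stricter: the last intake "must have taken place more than 14 days previously (phase 1b").
- **When the criteria apply.** Participants and recruitment: "Participants must meet the following inclusion criteria at the time of the screening visit".
- **Consent and screening.** Trial protocol gives screening the first 2 weeks, "starting on the day the subject signs the Informed Consent Form". The Fig 1 caption says that patients "will undergo a screening period (v1) with a maximum duration of 2 weeks", followed by randomization at v2.
- **Total duration.** Trial protocol: "Subjects will participate for up to 5 weeks".
- **Latest time for consent.** Participants and recruitment requires written consent "Prior to the start of medication in the study". It places the giving of full information after the eligibility criteria have been checked.
- **Risk.** The overview of clinical management in the Introduction describes withdrawal as the main hazard of oral baclofen. It names hyperthermia, seizures and psychic symptoms, and warns that spasticity can rebound severely.

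**The concern.** A withdrawal made only so that a patient can enter the trial is a trial procedure, and written consent should come before it. Here the stated timings place the withdrawal first and the signature at least two weeks later. In that interval the patient would carry the withdrawal risks that the article describes without having signed, without the full information step, and outside the period that the article counts as participation. The section on risks and unblinding procedures does not fill the gap, because its plan for worsening spasticity covers worsening under the study treatment.

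What is at stake is patient protection in phase 1b. It is not the validity of the dose-finding or of the phase 2b comparison.

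**Working it through.** No power or error-rate formula applies. The check is timeline arithmetic with the day of signature as day 0.

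**1. Reproduce the stated duration.** Screening 14 days + treatment 14 days + post-treatment 7 days = 35 days = 5 weeks. This matches the article. Time left for a consented washout: 35 − 35 = 0 days.

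**2. Place the washout.** Screening begins on day 0. A drug stopped 14 days before screening is stopped on day −14 at the latest. If more than 14 days is read strictly in whole days, that becomes day −15. Either way the whole washout lies before the signature.

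**3. Test whether the washout could fit inside screening.** Suppose that the patient signs on day 0, stops the drug that day, and has the screening visit as late as possible.
- Latest possible visit: day 14, because screening lasts at most 2 weeks.
- Time off drug needed at that visit: more than 14 days, so at least 15.
- 15 > 14, so this fails, though only by one day.

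The wording also speaks against this reading. The washout is timed before screening in two places and nowhere before randomization. The Fig 1 caption labels the screening period itself v1 and describes no consent visit before it.

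**4. Look for an earlier consent step.** The only deadline given for the signature is before study medication. The only earlier contact described is a telephone check of the main criteria for patients referred by associations, and consent is not mentioned there. Information follows the eligibility check, and being off myorelaxants is one of the criteria checked. Read literally, a patient still on the drug would have to complete the washout before reaching the information step.

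**5. Is a real withdrawal meant?** The sentence in Trial protocol says that participants must stop. The pharmacokinetic item under Outcome measures has plasma baclofen measured to check the washout. Both fit an actual withdrawal better than a mere filter for patients who are already off drug.

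**6. How many patients.** Phase 1b includes at most 30 subjects (Justification of sample size). The article does not say how many would stop a drug for the trial, so the range is 0 to 30.

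**7. What moving the consent changes.** These figures assume a 15-day minimum washout and no taper.

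| Quantity | As written | Consent before washout |
|---|---|---|
| Days off drug before signature | 15 | 0 |
| Participation from signature, at most | 35 days | 15 + 35 = 50 days |
| Total time off drug, at most | 15 + 35 = 50 days | 50 days |
| Baseline (last value before randomization), days after stopping | 15 to 15 + 14 = 29 | 15 to 29 |

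Only the first two rows change. If 14 days off drug were accepted as enough, the 15 in the first row would be 14 and participation would be 14 + 35 = 49 days.

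**The case against.** **The sentence may only restate eligibility.** It sits beside a phase 2b condition that looks back over the patient's medication, and the criteria themselves only require the patient to be off drug at screening. On that reading nobody is told to stop. This is possible, and it is why the number concerned may be 0. It does not remove the point, because the sentence speaks of stopping and the article plans a laboratory check of the washout.

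**The article is condensed.** The full protocol may hold a pre-screening consent or a supervised taper, and the consent deadline in the article does not forbid an earlier signature. This stands and lowers confidence. However, the finding does not rest on a missing detail. The article fixes the consent day, the washout time and the total duration, and these three do not fit together for a patient who stops for the trial.

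**The named risks belong to baclofen.** This stands too. The article does not say how many candidates take oral baclofen rather than another oral myorelaxant.

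**Stronger readings to avoid.** A reader might infer that patients are in fact being withdrawn without consent. The article shows only what follows if its wording is applied literally, and nothing in it reports such a case. A reader might also infer that all phase 1b patients are concerned, or that intrathecal baclofen is stopped for the trial. Patients already off drug are untouched, and for phase 1b intrathecal baclofen appears only as an entry criterion, with no instruction to stop it. Nor does the order of consent and washout bias the baseline or the dose-finding, since the time from stopping to baseline is the same either way.

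**Conclusion.** The point holds for one group: phase 1b patients who stop an oral myorelaxant in order to take part. On the stated timings their withdrawal precedes written consent by at least 14 days, and the 5 weeks of participation leave 0 days for it. The number concerned is between 0 and 30 and cannot be narrowed from the article. Phase 2b asks for stable medication and is unaffected.

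The conclusion assumes that the sentence on stopping describes a real withdrawal and that no earlier consent step exists in the full protocol. Confidence is moderate on both counts. The matter should be fixed because the article itself describes serious consequences of stopping baclofen and the correction is cheap. It is a consent and safety matter; sample size, eligibility criteria and analysis are not touched.

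**What to change.** Change three places together.

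1. **Participants and recruitment, consent paragraph.** Give full information and obtain written consent before any oral myorelaxant is withdrawn for the trial, and before study medication. Confirm the remaining inclusion and exclusion criteria at the screening visit after the washout. Moving the signature alone would not be enough, because the present text gives information only after the criteria are checked.
2. **Trial protocol, concomitant medication.** In step 1, participants who take an oral myorelaxant stop it after signing, under the supervision of the clinical team, so that the last intake is more than 14 days before the screening visit. This also brings the sentence into line with the inclusion criterion.
3. **Trial protocol, timeline, and the Fig 1 caption.** For these patients the screening period of up to 2 weeks starts at the screening visit after the washout. Participation is about 7 weeks: a minimum washout of 15 days plus up to 35 days makes 50 days, and any taper adds its own length. The statements that both phases share one schedule should carry this exception. All other patients stay at up to 5 weeks.

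If the full protocol already provides an earlier consent step, it is enough to state it in these places.

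**Cost.** Protocol and consent wording, and about 2 more weeks of participation for those who need a washout. Some consented patients will stop their drug and then fail screening. That can already happen as the text stands, but before consent.
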